### Participant screening and selection

2.2

The cases for this study were sourced from a real-world postoperative EC registry platform. This study pre-integrates advantageous units from Chinese medicine EC research (Additional file 1. Attended hospitals), including oncology advantageous departments in general hospitals and specialized gastrointestinal oncology advantageous departments. The goal was to standardize and collect clinical information on postoperative patients with EC and build a postoperative EC registry platform. This platform will support evidence-based studies by providing a comprehensive case database.

Based on the characteristics of the primary target population of QZYLP identified in the previous study, postoperative patients with EC from the registry platform were selected according to the following criteria:

Diagnostic criteria for EC were based on the *Guidelines of the Chinese Society of Clinical Oncology (CSCO) for Esophageal cancer 2021* (16). Pathological staging criteria follow the *World Health Organization (WHO) Classification of Tumors of the Digestive System, 5^th^ edition* (17). TNM staging criteria refer to the *Cancer of the Esophagus and Esophagogastric Junction: An Eighth Edition Staging Primer* (18). For patients who met the diagnostic criteria, the inclusion and exclusion criteria (listed below) were reassessed. Patients will not be recruited if they do not meet any of the inclusion criteria or meet any of the exclusion criteria.

### Inclusion criteria

2.3

EC without esophagogastric junction pT_1-4a_N_+_M_0_ (stage IIB-IVA) that met the diagnostic criteria without recurrence or distant metastasis;Patients who completed adjuvant therapy (including adjuvant radiotherapy, chemotherapy, chemotherapy + radiotherapy) within 6 months after R0 resection for EC.ECOG score 0–2.18–75 years old.Expected survival ≥ 3 months.Participants who voluntarily signed informed consent.

### Exclusion criteria

2.4

Presence of primary tumor at other sites.Patients with severe primary diseases affecting the heart, cerebral vessels, liver, kidney, or hematopoietic system.Patients with mental illness and mental and language impairments.Participation in other clinical trials within the past 3 months.Patients with known hypersensitivity or intolerance to study drug.

### Drop out criteria

2.5

Patients who are unable to adhere to the treatment owing to unforeseen events during the study.Participants who voluntarily request to withdraw from the study.Participants with poor adherence to the study protocol as determined by the investigator.Pregnancy, death, or loss of contact with the participant.

Following termination of treatment or withdrawal from the study, they entered a follow-up period. They received periodic follow-ups (every 3 months, with telephone follow-up accepted) to assess survival status, extending for at least 3 years post-operation.

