### Study design

2.1

This study is a multicenter, randomized, double-blind, placebo, parallel-controlled clinical trial conducted according to the protocol approved by the Medical Ethics Committee of Guang’anmen Hospital (2022-200-KY-01). It was registered with Clinical Trials (https://clinicaltrials.gov/) under the number NCT05626309. A randomized design is implemented using a centralized randomization system to conceal protocol allocation. The control group receives a placebo, while the experimental group is treated with QZYLP granules. Both groups also undergo conventional symptomatic therapy. Treatment duration spans 6 months, with follow-up continuing for 3 years post-surgery. After completing the final treatment or reaching the endpoint event, all patients entered a post-treatment follow-up period with evaluation every 3 months. The primary endpoint is the 1-year DFS rate after surgery, which is used to measure the proportion of patients who do not experience recurrence, metastasis, or death (from any cause) within 1 year following surgery. **Figure 1** shows the timeline for enrollment, intervention, and evaluation, while **Figure 2** shows the timeline for intervention and follow-up. **Table 1** depicts the study flowchart.

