**Figure 2 f2:**
[figure not shown]
Intervention and follow-up flow chart.

**Table 1 T1:** Flowchart of treatment phases.

Project		Lead-in period	Intervention period				Follow-up period
Timepoint		1	End of the first course of treatment	End of the second course of treatment	End of the third course of treatment	End of the N course of treatment	N+X
Week		-W1-W0	W4-W5	W8-W9	W12-W13	W4N-W4N+1	Every 3 months
Inclusion/exclusion criteria		✓					
Informed consent		✓					
Medical history							
Demographic data		✓					
Diagnosis		✓					
Therapeutic observation							
Vital signs		✓	✓	✓	✓	✓	
Clinical examination		✓	✓	✓	✓	✓	✓
Physical condition score		✓	✓	✓	✓	✓	✓
Clinical symptoms		✓	✓	✓	✓	✓	
Description of tongue and pulse		✓	✓	✓	✓	✓	
TCM syndrome		✓	✓	✓	✓	✓	
Imaging Examination	PET-CT/CT	✓			✓	✓	✓
	MRI、B-ultrasound	*			*	*	*
	Bone scanning	*			*	*	*
	Gastroscope	*			*		*
Tumor marker		✓	✓	✓	✓	✓	✓
Indexes related to fat distribution		✓	✓	✓	✓	✓	✓
MDASI-TCM		✓	✓	✓	✓	✓	
QLQ-QES18		✓	✓	✓	✓	✓	
Safety observation							
Routine blood tests		✓	✓	✓	✓	✓	✓
Liver/kidney function		✓	✓	✓	✓	✓	✓
Routine urine/stool tests		*	*	*	*	*	*
ECG		✓	✓	✓	✓	✓	✓
CTCAE			✓	✓	✓	✓	
Other work							
Drug combination			✓	✓	✓	✓	
Efficacy evaluation			✓	✓	✓	✓	✓
Treatment							✓

**Table 1** The schedule of participants. *Indicates: This examination is optional. For imaging examinations, the same examination method should be used for screening of the same site and for each review after enrollment, and the examination should be reviewed every 3 sessions during the treatment phase and every 3 months during the follow-up phase. Head, chest, and abdominal examinations should be selected as appropriate. If CT/MRI examination has been done for the same site, abdominal X-ray examination and ultrasound examination are not necessary. Bone scanning examination is selected according to the patient’s condition. TCM, Traditional Chinese Medicine. PET-CT, Positron Emission Tomography Computed Tomography. CT, Computed Tomography. ECG, Electrocardiogram. MRI, Magnetic Resonance Imaging. MDASI-TCM, M.D.Anderson Symptom Traditional Chinese Medicine. QLQ-QES18, Quality of Life Questionnaire of Oesophageal-Specific Module 18. CTCAE, Common Terminology Criteria for Adverse Events. ✓ Indicates: This work needs to be performed.

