#### Primary outcome

2.11.1

1-year DFS rate: Refers to the proportion of patients who did not experience recurrence, metastasis, or death (from any cause) within 1 year following surgery. Although OS is the gold standard for evaluating malignant tumor treatment, given the strong correlation between DFS and OS and to control of time costs, the 1-year DFS rate was selected as the primary endpoint to explore long-term efficacy (22).

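### Section 2.5 lists death, a primary-endpoint event, as a drop-out reason, and its follow-up of drop-outs conflicts with Section 2.1 and Table 1, so recurrences can be missed

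*Protocol article*

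**What the plan says.** The primary outcome (Section 2.11.1) is the 1-year DFS rate, defined as "the proportion of patients who did not experience recurrence, metastasis, or death (from any cause) within 1 year following surgery". Section 2.1 gives the same three event types.

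Section 2.5 (Drop out criteria) puts several different situations in one list: being unable to keep to treatment, the patient's own request to leave, "Participants with poor adherence to the study protocol as determined by the investigator", and "Pregnancy, death, or loss of contact with the participant". For patients whose treatment has ended or who have withdrawn, it continues: "They received periodic follow-ups (every 3 months, with telephone follow-up accepted) to assess survival status". This lasts at least 3 years after the operation.

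Two other places describe follow-up differently. Section 2.1 says that after the last treatment or an endpoint event "all patients entered a post-treatment follow-up period with evaluation every 3 months". In Table 1 the follow-up column is ticked for PET-CT/CT, clinical examination and efficacy evaluation, and the footnote says of imaging that "the examination should be reviewed every 3 sessions during the treatment phase and every 3 months during the follow-up phase". Neither place exempts patients who dropped out.

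**The concern.** There are two separate problems.

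The first is classification. A death within 1 year of surgery is a primary-endpoint event under Sections 2.1 and 2.11.1 and a drop-out under Section 2.5. The label matters because Section 2.9 adds patients to make up for drop-outs, and Section 2.14 decides case by case whether missing values count as drop-outs.

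The second is ascertainment. Section 2.5 does not separate a patient who stops the granules from one who leaves the study. The only purpose it names for later contact is survival status, and a telephone call is enough. Such a call can establish that a patient is alive but does not establish freedom from recurrence or metastasis. A site could therefore follow Section 2.5 faithfully and not look for the other two components of the endpoint.

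The timing makes this relevant to the primary analysis. Patients complete adjuvant therapy within 6 months of surgery (Section 2.3) and then take six 4-week courses (Section 2.10). For a patient who starts soon after adjuvant therapy, that is at most about 26 + 24 = 50 weeks from surgery, so stopping during treatment would fall before the 1-year reading. Patients who stop or adhere poorly may include some whose health is already declining, so missed recurrences could be related to prognosis. No choice of analysis set recovers a recurrence that was never looked for.

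**Working it through.** **Setting the passages side by side**

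| Question | Section 2.5 | Elsewhere in the article |
|---|---|---|
| Is death an event? | A drop-out reason | A primary-endpoint event (2.1, 2.11.1) |
| Purpose of follow-up contact | Survival status | Evaluation (2.1); efficacy evaluation (Table 1) |
| Form of contact | Telephone accepted | Clinical examination and PET-CT/CT ticked (Table 1) |
| Who is covered | Patients off treatment or withdrawn | All patients (2.1); no exemption (Table 1) |

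On the first row the article contradicts itself. On the other rows it gives two standards and does not say which governs.

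**Checking the planning model used for the illustration**

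Inputs from Section 2.9: control median DFS 19.3 months, gain 12 months (test median 31.3), 80% power, 24 months of uniform accrual, 36 months in total. Alpha is 0.05, two-sided according to Section 2.14. Exponential DFS is an assumption.

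- Hazard ratio = 19.3/31.3 = 0.617.
- Events (Schoenfeld) = 4(1.960 + 0.842)²/(ln 0.617)², rounded up to 135.
- Event probability = 1 − [exp(−12λ) − exp(−36λ)]/(24λ), with λ = ln 2/median: 0.564 (control) and 0.405 (test).
- Patients per arm = 135/(0.564 + 0.405) = 139.2, i.e. 140. This matches the stated 140.
- With 10% drop-out: 140/0.90 = 155.6, against the stated 155.

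The exponential model reproduces the plan's sample size, so it is a fair basis for an illustration.

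**One-year figures under that model**

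- Control DFS = exp(−12 ln 2/19.3) = 65.0%, event risk q_c = 0.350.
- Test DFS = exp(−12 ln 2/31.3) = 76.7%, event risk q_t = 0.233.
- Difference = 11.7 points.
- Expected events at 155 per arm = 54 + 36 = 90.

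**Effect of unseen events**

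Let d be the drop-out proportion in an arm, r the event risk of drop-outs relative to their arm, and s the share of drop-outs' events that goes unseen. Then

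observed difference = (q_c − q_t) − s × r × (d_c q_c − d_t q_t).

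The values of r and s are assumptions. So are the arm-specific values of d, except that 10% is the overall allowance in Section 2.9 (31 of 310 patients). The ranges use r = 1 to 1.5 and s = 0.7 to 0.9.

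| Drop-out, control / test | True difference (points) | Observed difference (points) |
|---|---|---|
| 10% / 10% | 11.7 | 10.1 to 10.9 |
| 5% / 15% | 11.7 | 12.9 to 14.0 |
| 15% / 5% | 11.7 | 6.2 to 8.8 |
| 5% / 15%, s = 0.8 | 0 | 2.8 to 4.2 |
| 10% / 10%, s = 0.8 | 0 | 0 |

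For example, with equal drop-out, r = 1 and s = 0.7: 11.7 × (1 − 0.07) = 10.9. With no true effect and both risks at 0.350: 0.8 × 0.350 × (0.15 − 0.05) = 2.8 points, and × 1.5 = 4.2 points.

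With 10% drop-out in each arm and r = 1, about 9 of the 90 events fall in drop-outs, of which 6 to 8 would be unseen. With r = 1.5 the figure is about 9.5 to 12.

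The illustration gives every patient a full 12 months at risk. Enrolled patients are free of recurrence when they enter after adjuvant therapy, so fewer events may occur inside the trial before 1 year, and the effects would shrink accordingly.

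**The case against.** The strongest reply is that this is loose wording and not a reduced schedule. Section 2.5 says that these patients enter a follow-up period every 3 months. Table 1 defines that period, with imaging and efficacy evaluation ticked. The sentence in Section 2.5 starts from the end of treatment or withdrawal, so read literally it could even cover patients who completed all six courses. A list that puts pregnancy, death and loss of contact together can also be read as reasons why participation ends, with no consequence for the analysis.

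Much of this stands, and it rules out several stronger readings that a reader might infer:

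- **That drop-outs are followed for survival and nothing else, so recurrence is not collected.** Section 2.5 does not say this is the sole purpose, and Section 2.1 and Table 1 point the other way. The documents support a conflict, not a settled omission.
- **That deaths are lost.** Survival is exactly what Section 2.5 follows, and death counts as an event in Sections 2.1 and 2.11.1. Deaths in patients who can be reached would be known. The fault is one of classification.
- **That the comparison is no longer by randomised group.** Section 2.14 plans a Full Analysis Set analysis, and nothing says that drop-outs are excluded or censored. Those definitions may sit in the full protocol or analysis plan, and their absence here is no finding.
- **That a benefit would be inflated.** This needs unequal drop-out or unequal risk between arms. The trial is double-blind, and the article gives no reason to expect either. With equal drop-out and equal relative risk, a true difference is diluted.

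The reply does not remove the contradiction itself. A site reading Section 2.5 on its own has no instruction to look for recurrence in these patients.

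**Conclusion.** The point holds as an internal inconsistency that affects how the primary endpoint is ascertained. Section 2.5 contradicts Sections 2.1 and 2.11.1 on death. It merges stopping drug, poor adherence and leaving the study, and it conflicts with Section 2.1 and Table 1 on what follow-up is for. If sites act on Section 2.5 as written, recurrences or metastases can be missed, possibly in relation to prognosis.

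Bias is a risk here, not a demonstrated loss. Under the stated assumptions, the planned 11.7-point difference falls by about 1 to 1.5 points with 10% drop-out in each arm, and a spurious difference of about 3 to 4 points appears under no effect if drop-out is 5% in control and 15% in test. These figures rest on exponential DFS and on assumed drop-out rates, drop-out risk and shares of unseen events. The article gives drop-out only as an overall 10% allowance, not tied to 1 year or to either arm. They show plausible scale only. The correction is worthwhile because missed recurrence dates are hard to recover later.

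**What to change.** 1. Remove death from Section 2.5 and state that it is a DFS event.
2. Split the section into two categories: discontinued study drug, and withdrew consent to follow-up. Treat loss of contact as a follow-up status, recorded with the date of last known disease status.
3. Reconcile Section 2.5 with Section 2.1 and Table 1, so that every randomised patient who has not withdrawn consent to follow-up stays on the 3-monthly recurrence schedule the article already contains. Record the date of any recurrence or metastasis as well as survival. Where contact is by telephone, obtain outside imaging reports.
4. State that investigator-judged poor adherence affects membership of the per-protocol set only.

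The cost is protocol and case report form wording plus a note to sites. The 3-monthly contacts and follow-up imaging are already planned, so the main extra work is chasing outside reports. The Trial status section says that recruitment is being extended, so sites that are still enrolling or following patients could apply the change.

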### Randomization

2.6

Central and compartmentalized randomizations were conducted using the Interactive Web Response System (IWRS) to ensure allocation scheme concealment. The test and control groups were randomized in a 1:1 ratio through the central randomization grouping method. Using R software (V3.3.3), three cycles of random statements were employed to generate random sequences, creating a list of random codes corresponding to serial numbers 001–310. Researchers accessed the central randomization system website, inputting necessary details (such as center number, patient initials, and contact phone number), and the system generated group assignments and corresponding random numbers for the cases. The protocol was followed based on the assigned groupings. If a participant inadvertently used the wrong group of drugs, no corrections were made, and the original drug treatment regimen was maintained. Details of the drug treatment were recorded in the case report form.

### Blinding

2.7

This is a double-blind study, ensuring that the investigator and participants remained unaware of the study details. Statisticians who are not involved in the clinical trial conducted the blinding process. The random code table, created by the research unit, was securely sealed and stored separately. The study drugs were manufactured, packaged, and supplied by Jiangyin Tianjiang Pharmaceutical Co., with the randomization code serving as the unique identification code for participants. Supervisors and outcome evaluators remained blinded throughout the study.

### Emergency blindness breaking

2.8

For this trial, a dedicated “emergency letter” system was established, where each drug was assigned a specific emergency letter. The actual treatment group (test/control) corresponding to each drug was indicated in a specific area of the emergency letter, covered by a disposable, fragile coating. Emergency unblinding was only performed in the event of a participant emergency where managing the situation required clarification of the medication used. In the event of an emergency requiring unblinding, the investigator will consult with the center in charge. Upon receiving signed approval, the investigator can open the emergency blinding letter and record the event. The unit in charge will be notified within 24 h after the unblinding.

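### Section 2.8 requires consultation and signed approval before the emergency letter may be opened, so access to the treatment code may be delayed when care depends on it

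*Protocol article*

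**What the plan says.** Section 2.8 (Emergency blindness breaking) sets up a system of letters in which "each drug was assigned a specific emergency letter". The treatment group sits under a fragile, single-use coating.

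The section then gives four statements about use:

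- The condition: "Emergency unblinding was only performed in the event of a participant emergency where managing the situation required clarification of the medication used".
- The first step: "In the event of an emergency requiring unblinding, the investigator will consult with the center in charge".
- The second step: "Upon receiving signed approval, the investigator can open the emergency blinding letter and record the event".
- The step afterwards: "The unit in charge will be notified within 24 h after the unblinding".

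**The concern.** Two controls are stacked in front of the letter. The first is the emergency condition, which already excludes unblinding out of curiosity or convenience. The second is a written approval, and it applies only to cases that have passed the first. By then the plan itself has accepted that management depends on the answer.

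What is at stake is the participant's care. An investigator facing such an emergency must either wait for the signature or open the letter and depart from the protocol. A plan should not force that choice. Nothing here bears on the estimate of treatment effect; the weight of the point is safety alone.

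**Working it through.** No arithmetic applies. The check is the order of the steps, a search for another route to the code, and a test of whether the conclusion depends on who the approver is.

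**Order of steps in Section 2.8**

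| Step | Requirement | Time limit stated |
|---|---|---|
| 1 | Emergency in which management depends on knowing the drug | not applicable |
| 2 | Investigator consults the center in charge | none |
| 3 | Signed approval received; the letter may then be opened and the event recorded | none |
| 4 | Unit in charge is notified | 24 h, counted from the unblinding |

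Consultation is worded as something the investigator will do, and permission to open follows receipt of the approval. Steps 2 and 3 therefore come before access. The single time limit belongs to step 4 and does nothing to shorten steps 2 and 3.

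**Search for another route**

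- Section 2.6 (Randomization): the web response system assigns groups and random numbers. No unblinding function is described.
- Section 2.7 (Blinding): the random code table is sealed and stored separately. Supervisors and outcome evaluators stay blinded.
- Section 2.12 (Adverse events): the investigator judges whether the participant continues. No access to the code is mentioned.
- Section 2.15.2 (Monitor): the monitor's duties include storing the blinding code. No emergency access is described.

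As the article is written, the letter is the investigator's only described route, and it lies behind the approval.

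**Does the conclusion depend on the approver?** The section names a center in charge before opening and a unit in charge afterwards, and does not say whether they are the same.

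- *Same body.* It has already approved in writing, so the later notice tells it little that is new. The approval may have to come from outside the site.
- *Different bodies.* Approval could be local and quick, and the notice to a second body makes sense. The signature still comes before opening.

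The possible delay differs between the two readings. The order of steps does not.

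**Reach.** The rule applies to 310 planned participants at 10 hospitals (Abstract, Methods) while they take study drug, which Section 2.10 sets at six courses of 4 weeks, 6 × 4 = 24 weeks. This is the population covered by the rule. It is not a count of people harmed, and the article gives no expected number of emergency unblindings.

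**The case against.** A reader might infer more than the text supports, and the case against those inferences is good.

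- *That the site cannot learn the treatment in time.* The article gives no turnaround for the approval. The investigator opens the letter, so once approval is given no further request for the code is described. The text supports a possible delay, not a certain failure.
- *That the approver is remote.* The two different terms fit a local sign-off at the participating center followed by notice to a lead unit. The remote reading cannot be excluded, but neither can it be assumed.
- *That the section contradicts itself* by asking for approval first and notice afterwards. This follows only if one body receives both, which is not stated.
- *That the signature defeats the purpose of the letters.* The section does not state their purpose or where they are kept. Immediate access is a plausible purpose, but it is the reader's inference.
- *That the delay has no upper limit.* The signatory, an out-of-hours contact or a fallback may sit in the full protocol or in the standard operating procedures that Section 2.15.1 mentions. A condensed article is not at fault for leaving these out.

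It is also fair to note that the Introduction reports no serious adverse effects with the prescription in the earlier study. That may mean few emergencies, but it does not show there will be none.

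All of this narrows the point. It does not remove it, because the criticism is of a rule the article states, not of detail it leaves out. Operating procedures might name who signs, but the published sentence would still put the signature first.

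**Conclusion.** The point holds in this limited form: opening the emergency letter depends on prior consultation and signed approval, although unblinding is already confined to emergencies in which management requires the information. The article states no exception, so access to the code may be delayed when it is needed.

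The length of the delay cannot be given. It depends on who approves and how quickly, and the article settles neither. It could be trivial if the approver is on site, and material if not. The frequency is also unknown.

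The conclusion assumes that sites follow Section 2.8 as published and that no document outside the article permits opening before sign-off. If such a provision exists, the remaining task is to bring the published wording into line with it.

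This is an inexpensive safety improvement. It does not affect the endpoint, sample size, error rates or analysis.

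**What to change.** Remove signed approval as a precondition in Section 2.8. State that:

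- the investigator may open the letter when the stated emergency condition is met, consulting the center in charge beforehand where feasible;
- the investigator records date, time, reason and signature;
- the unit in charge is notified within the existing 24 h;
- outcome evaluators remain blinded, as Section 2.7 already requires.

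In the same edit, say whether the center in charge and the unit in charge are one body or two.

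The cost is one sentence in the protocol and a memo to sites. Section 4 (Trial status) says recruitment would run beyond August 30, 2024, so the memo could still help any participant on study drug. The downside is a slightly higher chance of an unnecessary unblinding. The emergency condition, the written record, the 24 h notice and the continued blinding of outcome evaluators limit that risk.
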